## Abstract

**Introduction:**

Joint bleeds are the most significant complication in haemophilia, leading to functional impairment and reduced quality of life. Repeated bleeding during early childhood can cause severe physical limitations in adulthood. Early detection of joint damage, combined with therapeutic interventions, has a huge impact on mobility, physical health and long-term quality of life.

**Methods and analysis:**

A novel markerless video motion analysis method using deep neural networks will be explored in this single-centre, prospective, longitudinal pilot feasibility study. The study will include children and young adults with haemophilia, as well as age-matched healthy controls. Standardised video recordings, the Haemophilia Joint Health Score (HJHS), clinical data, accelerometer-based physical activity tracking and questionnaires on quality of life and activity levels will be collected at baseline and after 12 months.

For haemophilia patients, individual consultations will be held after each assessment to discuss joint health and possible interventions. Results will be compared with those of healthy participants to assess the method’s feasibility and to explore outcome differences and correlations. The primary focus will be on evaluating the study’s feasibility, practicability, acceptance, possible risks and data quality with regards to a potential future multicentre trial.

**Ethics and dissemination:**

The study was approved by the local Ethics Committee at the Medical Faculty and the University Hospital Tübingen (project No. 188/2023BO1, approval 5 July 2023, protocol version 2.1) and registered at the German Clinical Trials Register (registered 22 September 2023, https://drks.de/search/en/trial/DRKS00032707). Results will be shared at conferences and in peer-reviewed journals.

This pilot study will explore the feasibility, practicability and acceptance of a protocol using artificial intelligence in gait analysis to identify patients at risk of early joint damage and to monitor the functional status of children and young adults with haemophilia in routine care.

**Trial registration number:**

German Clinical Trials Registry (DRKS00032707).

STRENGTHS AND LIMITATIONS OF THIS STUDYProspective longitudinal monocentric pilot study evaluating the feasibility, practicability and acceptance of quantitative and qualitative motion analysis in patients with haemophilia.Multimodal assessment combining markerless video-gait analysis, accelerometry, physical examination and patient-reported questionnaires.Innovative artificial intelligence-based assessment of video-gait analysis to test clinical application for the first time.Primary outcomes include recruitment rates, participant adherence and data quality to inform the design of a future multicentre study.Limitations include small sample size, single-centre design, high participant burden, potential bias in self-reports, uncertain adherence to accelerometry, and limited statistical power and interpretability due to heterogeneity.

## Introduction

 Haemophilia is an inherited bleeding disorder caused by a deficiency of clotting factor VIII or IX (haemophilia A or B).^1^ Patients, especially with severe haemophilia, experience recurrent joint bleeds from early childhood. Untreated or repeated bleeding into joints often results in haemophilic arthropathy, characterised by chronic pain, reduced mobility and long-term disability.^2 3^

Early diagnosis of joint damage and timely intervention—such as physiotherapy, factor replacement and orthopaedic care—can significantly improve mobility and quality of life.^4^,^6^ Nevertheless, subtle joint impairments often go unnoticed, especially in small children, leading to compensatory gait patterns and reduced physical activity.^4 7^

Physical activity plays a critical role in the development and long-term health of children with haemophilia.^5 8 9^ However, many patients remain less active than their healthy peers due to pain, fear of injury and lack of treatment coordination.^10^

Despite advances in treatment, haemophilic arthropathy remains a major burden, and joint function must be regularly assessed.^9 11 12^ Standard clinical assessments, such as visual gait observation and the Haemophilia Joint Health Score (HJHS),^13 14^ are either subjective or limited in detecting early impairments. While 3D gait analysis offers precise data on joint movement relevant to everyday life, it is costly, time-consuming and impractical for routine care, especially in paediatric settings.^15^,^19^

Recent advances in artificial intelligence (AI) and video technology enable qualitative, cost-effective and markerless video gait analysis using standard cameras. Deep neural networks can identify anatomical landmarks and gait events, enabling automated calculation of joint angles and gait parameters. This method offers a scalable and accessible alternative to 3D analysis, especially in children.^20 21^ Markerless video gait analysis is comparable regarding accuracy, validity and reliability to marker-based 3D gait analysis in spatiotemporal parameters^22^ even in small children.^23^ Additionally, the meta-analysis showed that kinematic parameters for the hip and knee in the sagittal plane are generally valid and reliable. The angles for the ankle joint are, to date, less accurate than marker-based measurements, depending on the method used.^22^

The HJHS, as a standard clinical assessment tool, has limited sensitivity, resulting in high variability and uncertainty in interpreting changes over time.^24^ Therefore, more sensitive diagnostic tools are needed to detect subclinical joint changes before irreversible damage occurs.^24 25^ Markerless video gait analysis might offer a solution, addressing this critical need in haemophilia care by providing objective, non-invasive assessment of joint health.

Patient outcomes in haemophilia are influenced by various factors, including joint health, physical activity and quality of life. This study focuses on physical health and activity as potential contributing factors. Physical activity can be quantitatively assessed using wearable accelerometers that can objectively measure physical activity patterns in daily life, including intensity of activity and sedentary behaviour—factors closely linked to joint health and quality of life.^26 27^ However, studies using accelerometry in haemophilia are limited and suggest lower physical activity levels compared with healthy individuals.^28 29^ In addition, patient-reported outcome measures (PROMs) of daily activity levels and quality of life will be assessed by self-reported questionnaires.

Early detection of joint damage in haemophilia patients can decrease the disease burden. Therefore, markerless video gait analysis could reduce the time and cost to monitor functional joint status, making it suitable for routine clinical use and enhancing treatment management. The presented study aims to facilitate bridging the gap between highly specialised motion analysis methods and practical clinical monitoring in haemophilia patients and will lay the foundation for a future multicentre trial.

### Aim and objective

The aim of this pilot study is to test the feasibility, practicability and acceptance of the procedures for a quantitative and qualitative motion analysis for early detection of joint damage in haemophilia patients and to identify necessary adjustments for a larger, more comprehensive study.

To assess the feasibility of the study protocol, recruitment rates will be estimated and reasons for ineligibility or refusal will be analysed. The practicability and appropriateness of the study procedures and methods will be evaluated based on data on the proportion of usable video gait recordings, participants’ adherence to accelerometry, proportion of missing data, questionnaire completion rate, sensitivity of measurements to detect changes and unexpected problems during assessments. The acceptance of the study will be determined by evaluating the retention and the dropout rate.

This clinical trial has feasibility as its only primary objective. All clinical outcomes are considered exploratory. The main exploratory outcomes are the detection of early movement changes through markerless video gait analysis and the evaluation of joint health using the HJHS. Secondary clinical outcomes are anthropometric indices, clinical parameters, activity metrics from accelerometry and PROMs from questionnaires on daily activity and quality of life.

## Methods and analysis

### Study design and setting

This study follows a prospective, longitudinal design consisting of cases and controls and will be conducted over a period of 36 months (for details in study design, eligibility and interventions see table 1). It is designed as a pilot feasibility study primarily assessing feasibility, practicability and acceptance parameters as well as exploring selected clinical outcomes. All outcome parameters are listed in table 2 and described in detail in the following sections.

**Table 1 T1:** Study design, eligibility and interventions of the study protocol

**Study design**	
Methodological approach	Single-centre, prospective longitudinal pilot feasibility study including cases and controls
Sample size	24 patients (12 severe, 12 moderate haemophilia), 24 matched controls
Timeline	Four appointments for patients within 18 months, two appointments for matched controls within 12 months
Primary objectives	Feasibility
	Practicability
	Acceptance
Exploratory clinical outcomes	Parameters of markerless video-based gait analysis for the detection of joint changes over the course of 1 year
	Haemophilia Joint Health Score HJHS: Haemophilia Joint Health Score, MoMo-AFB: Motorik-Module Activity Questionnaire, EQ5DY5L: EuroQol 5-Dimension Youth 5-Level questionnaire (for children and adolescents), EQ5D5L: EuroQol 5-Dimension 5-Level questionnaire (for adults), Haemo-Qol: Haemophilia quality-of-life, HEP-Test-Q: Haemophilia & Exercise Project-Test-Questionnaire (HJHS)
Secondary clinical outcomes	Anthropometric measurements, clinical data
	Activity parameters from accelerometry
	Activity parameters from questionnaire (MoMo-AFB)
	Quality of life questionnaire (EQ5DY5L, EQ5D5L)
	Additionally, for haemophilia patients disease-adapted questionnaires (Haemo-Qol, HEP-Test-Q)
**Eligibility**	
Participants	Patients at the Department of Paediatrics and Adolescent Medicine of the University Hospital Tübingen aged >18 months suffering from severe or moderate haemophilia A or B or healthy participants matching one of the haemophilia patients
Inclusion criteria	Given informed consent
	Confirmed severe or moderate haemophilia or age- and sex-matched to an included patient
Exclusion criteria	No informed consent/relevant language barriers
	>30 years or <18 months of age
	Inability to walk a 50 m distance
	Control group: serious injury within the last 6 months, neurological, musculoskeletal diseases or joint complaints

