**Medical record data**	
Disease specific parameters	Disease severity
	Factor activity
	Traumas
	Therapy
	Quantity of factor administrations
	Secondary diagnoses
	Medical history and injuries, bleeding events
	Clinical, laboratory chemistry and imaging findings (as far as collected during routine care)

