### Participants and recruitment

Haemophilia care at the University Hospital Tübingen is provided through separate paediatric and adult divisions. Together, they manage approximately 30 patients with severe and 30 with moderate haemophilia, the majority of whom are children. The sample size for the feasibility pilot study is primarily guided by practical considerations.^30^ With a targeted recruitment rate of 40%, a sample size of 12 participants per group will be feasible. Methodological recommendations for feasibility studies suggest that samples of 12–30 participants per group are sufficient to assess feasibility outcomes such as recruitment rates, retention, data completeness and preliminary parameter estimates for future sample size calculations.^31^,^33^ Since the subgroups of severe and moderate haemophilia will be evaluated separately, the number of cases in each of these two groups is planned to be 12, resulting in a total of 48 participants (24 patients and 24 control subjects).

For each patient with haemophilia enrolled in this study, one healthy subject will be recruited to provide a normative reference dataset. The healthy subjects will be matched to the haemophilia patients based on age, gender, height and body mass. All patients of the Department of Paediatrics and Adolescent Medicine of the University Hospital Tübingen and healthy siblings from the age of 18 months will be able to participate in the study if they fulfil the inclusion criteria and none of the exclusion criteria applies (see table 1). Comparison with age-matched healthy controls will be essential due to the wide age range and heterogeneity of the study cohort. While most participants will be children, young adults will also be included to ensure a sufficient sample size in the moderate and severe haemophilia groups, given the rarity of the condition.

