### Statistical methods

Statistical analyses will be performed using SPSS Statistics 31.0.0 (IBM Corporation, Armonk, NY, USA). Feasibility as the primary outcome of this pilot study will be evaluated by calculating the percentage of people contacted (recruitment rate) and those who completed all assessments (refusal, retention and drop-out rate). The proportion of usable video gait recordings, participant adherence to accelerometry, proportion of missing data and questionnaire completion rate will be summarised. Reasons for ineligibility or refusal will be documented and interpreted by the research team to identify relevant topics (table 2). Data will be summarised using frequencies, percentages, means, SD, medians and ranges, as appropriate. CIs (95%) will be calculated for key feasibility parameters (eg, recruitment and retention rates) to estimate the precision of these outcomes. Patterns of missing data will be examined and reported.

As this is a feasibility study, participant characteristics and outcome measures will be examined for normality and summarised using appropriate tests. A table will be included to compare key demographic and clinical characteristics between the two patient groups and the healthy participants. Variance, SD and differences between the patient groups and the healthy participants in spatiotemporal and kinematic gait parameters, as well as in the HJHS, will be reported. Changes over time (baseline, follow-up and change from baseline) will also be calculated and compared. No a priori hypotheses will be tested; therefore, all p values are reported as descriptive measures. Associations and potential influences of age, physical activity and health-related quality of life on gait parameters and HJHS will be reported. These variables will either be included as covariates in the statistical analyses or explored through subgroup analysis, as appropriate. Where applicable, comparisons with age-specific healthy participants and reference values from the literature will be made.

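### Injury, neurological and musculoskeletal exclusions bind controls only, so patients with gait problems unrelated to haemophilia can bias the exploratory patient-control gait and HJHS differences

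*Protocol article*

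**What the plan says.** The eligibility part of Table 1 lists this exclusion: "Control group: serious injury within the last 6 months, neurological, musculoskeletal diseases or joint complaints". Its opening words confine it to controls. The only gait-related exclusion that also applies to patients is "Inability to walk a 50 m distance". The inclusion criterion is "Confirmed severe or moderate haemophilia or age- and sex-matched to an included patient", with no condition on other diseases that affect gait.

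Under Participants and recruitment, for each patient "one healthy subject will be recruited to provide a normative reference dataset". Matching there is on age, gender, height and body mass. The planned size is "24 patients (12 severe, 12 moderate haemophilia), 24 matched controls", and the two severity groups are to be evaluated separately.

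The Statistical methods section will report "Variance, SD and differences between the patient groups and the healthy participants in spatiotemporal and kinematic gait parameters, as well as in the HJHS". As covariates or subgroup variables it names age, physical activity and health-related quality of life. Table 2 lists traumas, secondary diagnoses and "Medical history and injuries, bleeding events" among the medical record data, and Table 1 has chronic disease, health impairments and injuries recorded at the appointments. No analytic use of these items is stated.

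**The concern.** Some asymmetry is unavoidable. Controls serve as a healthy reference, and joint disease caused by haemophilia is what the study wants to see in patients. The rule goes further than that. A condition with no link to joint bleeding bars a control but not a patient, so anything it does to gait or to the HJHS (which scores range of motion, strength and global gait, among other items) appears on the patient side only. The resulting bias points the same way as the effect of interest, and the comparison cannot tell the two apart.

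This matters because gait and the HJHS are the main exploratory outcomes. The Statistical methods section also puts the between-group difference in spatiotemporal gait parameters forward as the best measure for judging the programme, and in context that means patients against healthy participants. Participants and recruitment justifies 12 per group partly by the need for preliminary estimates for later sample size calculations. The Limitations section mentions heterogeneity, but ties it to the wide age range.

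**Working it through.** **The plan's own figure.** The size rests on recruitment: "With a targeted recruitment rate of 40%, a sample size of 12 participants per group will be feasible". With about 30 severe and 30 moderate patients under care, 0.40 × 30 = 12 per severity group, 2 × 12 = 24 patients, and with one control each 48 in total. This reproduces. No power, effect size or SD is stated, so the asymmetry alters no number in the article.

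**Assumptions.** The article gives neither the frequency nor the effect of unrelated gait conditions. Below, *n* is the patient group size, *k* the number of affected patients and *d* their distance from the other patients in SD units, towards worse function. The other patients and the controls are taken to have SD 1.

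1. *Chance of at least one affected patient*, 1 − (1 − p)^n:

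| Assumed frequency p | n = 12 | n = 24 |
|---|---|---|
| 2% | 22% | 38% |
| 5% | 46% | 71% |
| 10% | 72% | 92% |

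2. *Shift in the patient mean*, (k/n) × d. One patient among 12 gives 2/12 = 0.17 SD at d = 2 and 3/12 = 0.25 SD at d = 3. Over k = 1 to 3 and d = 1 to 2, the range is 0.08 to 0.50 SD at n = 12 and 0.04 to 0.25 SD at n = 24.

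3. *Expected patient variance with one affected patient among 12*, [10 + (11/12)(d² + 1/11)]/11:
 - d = 2: (10 + 3.75)/11 = 1.25
 - d = 3: (10 + 8.33)/11 = 1.67, an SD of 1.29

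4. *Sampling error for scale.* The 95% half-width for an unmatched difference in means is 1.96 × √(2/n): 0.80 SD for 12 v 12 and 0.57 SD for 24 v 24.

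5. *Effect on a later sample size*, which is proportional to variance/difference². Take d = 3 and 12 v 12. The pooled variance is (1.67 + 1)/2 = 1.33, and the apparent difference is the true one plus 0.25 SD.
 - For a true difference of 0.8 SD: 1.33/1.05² = 1.21, against 1/0.8² = 1.56. The ratio is 0.77, so the planned size is about 23% too small.
 - The two effects cancel where √1.33 × δ = δ + 0.25, that is at δ of about 1.6 SD. Above that the planned size is too large.

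**The case against.** The strongest reply is that the asymmetry mostly follows from the design. A reference group must be healthy, the patients represent the clinic population in which routine use is being tested, and the pool is only about 60 people. Musculoskeletal disease and joint complaints cannot be excluded from patients without removing the condition under study. What remains is a narrow group, and nothing in the article shows that any such patient attends this centre. Feasibility is the only primary objective, p values are descriptive, and all findings are labelled exploratory. All this stands, and it limits the point to a minor one. The illustrated shifts also lie inside the sampling error in step 4. They are systematic, however, so the interval does not reflect them.

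It can also be said that sensitivity analyses belong in an analysis plan that is not shown. That answers part of the remedy but not the cause, because the eligibility rule is fixed in this article.

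Three stronger readings are tempting, and the article does not support them:

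- *That the comparison is run on everyone enrolled.* The Statistical methods section refers only to patient groups and healthy participants and defines no analysis set.
- *That someone injured between month 0 and month 12 must enter the change from baseline.* The article is silent on events after entry. Removing people because of such an event could itself bias the change.
- *That a variance of 1.67 makes a later trial about two-thirds too large.* That takes one arm's variance alone and ignores the shift in the difference. Step 5 shows that for a two-group comparison the error can go either way.

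**Conclusion.** The point holds for the entry rule and the baseline comparison. Table 1 lets patients with gait-relevant conditions unrelated to haemophilia enrol while refusing controls with the same conditions, and neither the matching nor the named covariates offset this. If such patients enrol, the patient-control differences in gait and HJHS are biased in the direction expected of haemophilia and the patient SD is too large.

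On the illustrative assumption of one such patient 2 to 3 SD away among 12, the shift is 0.17 to 0.25 SD and the patient variance 1.25 to 1.67 instead of 1. The size depends wholly on assumed frequencies and effects. The article shows that such patients can enrol, not that they will, and it does not commit to attributing every deficit to haemophilia. Severity is minor: only exploratory estimates are affected, and the recruitment, retention and data-quality outcomes are untouched.

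**What to change.** Add a short rule to the Statistical methods section, with a pointer from Table 1:

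- From the baseline history already collected (secondary diagnoses, traumas, injuries), and without sight of the gait results, flag patients with a clearly non-haemophilic neurological or musculoskeletal disease, or with a serious injury in the last 6 months not due to a joint bleed.
- Keep flagged patients enrolled and in every feasibility rate.
- Report the patient-control differences and SDs for gait and HJHS twice: with all patients, and without the flagged patients and their matched controls.
- Base the flag on baseline only.

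No new data are needed, and nobody's enrolment or care changes. The restricted comparison loses perhaps one or two pairs. In a group of 12, the half-width 1.96 × √(2/n) rises from 0.80 SD to 0.84 SD with 11 pairs or 0.88 SD with 10. Deciding whether a condition is unrelated to haemophilia also takes some judgement, which is why the flag should be limited to clear cases and set before the gait results are seen.

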**Interventions**	
Interventions during appointment	Anthropometric measurements (length, weight, etc)
	Collection of clinical data (medical history, chronic disease, health impairments, injuries, etc)
	Collection of disease-specific parameters
	Assessment of HJHS (Haemophilia Joint Health Score)
	Recording video gait analysis
	Completing activity questionnaire (MoMo-AFB)
	Completing quality of life questionnaire (EQ5DY5L, EQ5D5L)
	Additionally, Haemo-Qol, HEP-Test-Q for haemophilia patients
	Handing out Actigraph and documentation protocol with a successive 8-day wear-time at home

EQ5D5L, EuroQol 5-Dimension 5-Level questionnaire (version for adults); EQ5DY5L, EuroQol 5-Dimension Youth 5-Level questionnaire (version for children and adolescents); Haemo-Qol, Haemophilia quality-of-life; HEP-Test-Q, Haemophilia & Exercise Project-Test-Questionnaire; MoMo-AFB, Motorik-Module Activity Questionnaire.

**Table 2 T2:** Applied tools and categories in the assessment

Tool	Categories
